## Abstract

**Background:** Managing repaired tetralogy of Fallot (TOF) patients is still challenging despite the fact that published studies identified prognostic clinical or imaging data with rather good negative predictive accuracy but weak positive predictive accuracy. Heterogeneity of the initial anatomy, the surgical approach, and the complexity of the mechanism leading to dilation and ventricular dysfunction explain the challenge of predicting the adverse event in this population. Therefore, risk stratification and management of this population remain poorly standardized. **Design:** The CMR/CT WG of the Italian Pediatric Cardiology Society set up a multicenter observational clinical database of repaired TOF evaluations. This registry will enroll patients retrospectively and prospectively assessed by CMR for clinical indication in many congenital heart diseases (CHD) Italian centers. Data collection in a dedicated platform will include surgical history, clinical data, imaging data, and adverse cardiac events at 6 years of follow-up. **Summary:** The multicenter repaired TOF clinical database will collect data on patients evaluated by CMR in many CHD centers in Italy. The registry has been set up to allow future research studies in this population to improve clinical/surgical management and risk stratification of this population.

## 1. Introduction

Tetralogy of Fallot (TOF) is the most frequent cyanotic congenital heart disease (CHD), with an incidence estimated at 1/3500 live births. The latter is represented by four distinctive features: a perimembranous ventricular septal defect (VSD), the aortic root that overrides the septum, and therefore also the VSD, accompanied by right ventricular (RV) hypertrophy, and right ventricular outflow tract (RVOT) obstruction; the latter derived from the malalignment and the anteriorly deviation of the conal septum. [1] Consequently, TOFs can be considered a cono-truncal malformation; in fact, due to this malalignment, the ventricular septum results anteriorly deviated, leading to an underdevelopment of the RV outlet portion of the RV, also known as infundibular, which results in an RV outflow that is narrowed and obstructed [1,2].

From the late 70s to nowadays, cardiac surgery has rapidly evolved and improved. This has permitted childhood intra-cardiac TOF corrections and has allowed the majority of the TOF patients (more than 90%) to survive to adulthood. This population of patients that underwent TOF cardiac surgery during childhood, live to date with a repaired TOF and may present with a wide range of residual anatomical/hemodynamic/thoracic residual issues, needing to be addressed in the future in their life. However, their optimal treatment is hampered by their heterogeneity due to significant differences in initial cardiac/pulmonary anatomy, surgical techniques of repair, as well as the era of them and subsequent surgical/interventional procedures along the follow-up [1,2].

The RVOT obstruction can occur at multiple levels (subvalvular, valvular, and supravalvular); therefore, it is very common that TOF may be accompanied by infundibular pulmonic stenosis and annular hypoplasia of the pulmonary valve, the main pulmonary artery, and branches, along with any peripheral pulmonary artery stenosis [2].

The surgical repair consists of the closure of the interventricular defect and relief of the obstruction of the right outflow tract, resecting the RV infundibular muscularity, and very often extending the incision to the pulmonary annulus, opening it utilizing a trans-annular patch. In more severe cases, pulmonary pathway-associated anomalies need to be addressed. All this, inevitably, causes severe pulmonary valve dysfunction that, together with an RV infundibulum negatively remodeled, leads to an RV overload [1,2,3,4].

In addition, ROVT aneurysmal dilatation, succeeding pulmonary regurgitation, anastomotic site stenosis, main/branches pulmonary arteries stenosis, and distortions, along with progressive aortic root dilatation and subsequent aortic regurgitation, biventricular failure, and residual VSD, are also possible as follow-up sequelae [1,2,3]. It is also estimated that in the long-term follow-up, 30% of patients with operated TF will have atrial arrhythmia and 10% will have complex ventricular arrhythmias (VT). In contrast, the risk of sudden death has been estimated at around 0.2%/year [2].

It is well known that the repair leads to right ventricular scarring and the extension of such myocardial fibrosis is documented on the cardiac magnetic resonance (CMR) by the presence of late gadolinium enhancement (LGE). Scar burden visualized by magnetic resonance imaging has been shown to be predictive for inducible VT in this population. In fact, myocardial fibrosis results in decreased myocardial contractility and relaxation, and serves as a potential substrate for scar-induced VT. Similarly, other measures such as myocardial strain and rotation patterns, location and extent of myocardial fibrosis, LV systolic circumferential strain rate, and other parameters derived from magnetic resonance all contribute to our understanding of higher-risk substrates for VT. Given that the method of performing the surgical correction has changed over time, from a transannular patch with a transventricular approach to that with a transatrial approach, the obvious consequence is that even the surgical era is also associated with risk of VT. Arrhythmias are the most important problem to be taken into consideration in TOF. It has been estimated that in the long-term follow-up of TOF patients, 30% of patients will have atrial arrhythmia and 10% will have complex ventricular arrhythmia, and the mortality risk triples after the third postoperative decade, with sudden cardiac death (SCD) being the most common cause of late mortality [2,3,4,5].

Pulmonary valve replacement (PVR) is recommended, at some moment of the patient’s life, as the best choice to resolve the RV overload due to pulmonary valve incompetence preventing the progressive exercise intolerance, arrhythmia due to the right heart failure, and sudden death. However, to this day, indications and optimal timing of PVR are unclear in the asymptomatic population, and the extent to which PVR really improves survival is still unknown since it does not completely eliminate right ventricular scarring. In addition, the bioprostheses valves used for PVR are destined to deteriorate in a short time, both for the structural valve failure and the increased risk for endocarditis [3,4,6].

Given all these premises, it is clear that many questions regarding the follow-up and late management, along with a risk stratification, of repaired TOF are still unanswered, with an imperative need to be addressed. Hence, the multicenter repaired TOF clinical database registry, that we here present, has been set up to allow future research studies in this population to improve clinical/surgical management and risk stratification of this population.

## 2. Materials and Methods

### 2.1. Trial Rationale

In clinical practice, the diagnosis and monitoring of any residual defects and adverse events in this population are based on clinical evaluation and ECG on non-invasive imaging diagnostic tools. Echocardiography remains the first-choice method; however, CMR is considered the method of choice for measuring volumes and functions (both atrial and mostly important ventricular) and evaluating pulmonary regurgitation and the distribution of flows in the pulmonary branches. Moreover, thanks to the ability to characterize the myocardium, CMR allows for evaluating both focal and diffuse myocardial fibrosis. Therefore, CMR has a pivotal role in the lifelong follow-up and decision-making process for the repaired TOF population [3].

A pulmonary valve of adequate size for the body surface, surgical or interventional implanted, is today the only therapeutic option to contrast progressive right ventricular dilatation. However, there is currently no valve or pulmonary conduit of lifelong duration. Therefore, multiple procedures are often necessary over a lifetime. In addition, there is no clear evidence that the pulmonary valve reduces arrhythmia or improves survival in this population [7].

Published studies identified prognostic clinical or imaging data with good negative predictive accuracy but weak positive predictive accuracy [3]. The increased risk of an adverse outcome was reported to be associated with progressive dilation and dysfunction of the left ventricle [8,9]. However, heterogeneity of the initial anatomy, the surgical approach, and the complexity of the mechanism leading to dilation and ventricular dysfunction explain difficulties in predicting the adverse event in this population [10,11,12].

Therefore, risk stratification and management of this population remain poorly standardized and debated. Also, there is a lack of knowledge of very long-term survival due to only 40–50 years of follow-up available for repaired TOF [13,14,15].

Multicenter clinical databases are helpful for the evaluation and the study of chronic diseases, reducing the heterogeneity of the population enrolled and improving the statistical empowerment [16].

The CMR/CT WG of the Italian Pediatric Cardiology Society clinical database of repaired TOF involves many pediatric cardiology centers managing and treating treatment CHD in Italy. Its aim is to collect a large cohort of repaired TOF anamnestic, clinical, imaging data, and adverse events. The study data will be included in further studies to contribute to identifying anamnestic and clinical-instrumental parameters predictive of adverse events in repaired TOF patients and, therefore, contribute to improving clinical and surgical management of this complex population.

### 2.2. Study Design

This observational study will include all eligible patients retrospectively and/or prospectively repaired TOF patients who were evaluated for a CMR study in participating in a CMR Lab from 1 January 2004 to 31 December 2024. Eighteen Italian CMR sites have accepted to participate in this study. Eight have already received the local ethical committee’s approval and started the data collection. The study has also been registered on ClinicalTrials.gov with the ID: NCT05288894. This study protocol also follows and adheres to the SPIRIT recommendations.

### 2.3. Inclusion Criteria

Patients with repaired TOF/pulmonary atresia + VSD, double outlet right ventricle (DORV);Age > 10 years, as CMR is indicated in younger patients only in exceptional cases.

### 2.4. Exclusion Criteria

Different associated complex pathology such as MAPCAs, atrioventricular canal or Ebstein;Incomplete CMR study;Patients who do not consent to the study;Contraindication to CMR.

### 2.5. Data Collection and Management

#### 2.5.1. The Software Platform for the Implementation of the Clinical Database

Data will be recorded into a web-based case report form that will be accessible through a restricted web-based site for the Fallot-CMR Multicenter Italian Database, developed as centralized support to the network of centers.

The multicenter repaired TOF clinical database is based on the Rare Diseases Platform (RDP), a software for clinical data management already used to develop and support other patient registries such as the Dravet syndrome Italian registry and European RESIDRAS Platform (REF); the Tuscany registry for development of mental and epileptic encephalopathies and medical comorbidities (REMEDIES) for the DECODE-EE project; and the celiac disease Tuscany registry.

RDP implements a web-based application, which allows different hospitals or research centers to manage a patient’s medical records. Medical records keep a patient’s clinical history, where some data can be entered once, and some are serials. As a rule, the investigator can access only the information associated with the medical records created and maintained within the hospitals.

However, to support the cooperation among centers, the information can be shared among hospitals with different approaches, i.e., one possible technique consists of requesting a medical record that is subsequently handed over to another hospital. Data extraction in tabular form is available for any managed entity where required data is pseudonymized to mask fields that could lead to the disclosure of personal data belonging to a single patient.

For the multicenter repaired TOF clinical database, the most relevant anamnestic, clinical, and imaging data of repaired TOF were identified.

The platform is designed to manage health data; hence, particular attention is paid to personal data protection. These requirements are addressed by the General Data Protection Regulation (GDPR), and the data are managed and stored according to the highest standards in data management.

Patients will be assigned a unique identification code by which they will be identified. The enrollment site will give the identification number after a patient consents to participate in the registry. The link between the patient and the associated identification number will remain at the enrolling center under restricted access.

Each participating center will be responsible for collecting demographic, anamnestic, clinical, and image data sets defined by this study. In addition, any adverse events in the follow-up will be organized.

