#### 2.5.3. Planned Analysis

The data collected would be suitable for longitudinal studies and outcome studies.

Any investigator can suggest a study by submitting the idea, starting with a hypothesis. The idea will be discussed among members and with the proponent/s. If the scientific committee accepts the idea, the dataset of the deidentified data needed for the study will be available to the proponent.

The mains endpoints collected in this clinical database will be:Sudden cardiac death;ICD implantation;Sustained ventricular arrhythmias;Non sustained ventricular arrhythmias;Atrial flutter, atrial fibrillation;Supraventricular tachycardia (SVT) consisted of an abrupt salve of three or more consecutive atrial premature beats at a rate of >100 beats per minute;Palpitations associated with syncope or near syncope in patients subsequently found to have inducible sustained SVT;Worsening of CMR data in particular dilation of the right ventricle, worsening of bi-ventricular function and heart failure.

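### Registration only after consent leaves sudden deaths between a CMR (from 2004) and consent uncaptured, so sudden-death risk counted from CMR is biased downward

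*Protocol article*

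**What the plan says.** Section 2.2 of the protocol article sets the population: "This observational study will include all eligible patients retrospectively and/or prospectively repaired TOF patients", "evaluated for a CMR study in participating in a CMR Lab from 1 January 2004 to 31 December 2024". The window is 21 calendar years long, and much of it lies before the article was written.

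Two rules govern entry. Section 2.4 lists among the exclusions "Patients who do not consent to the study". Section 2.5.1 says of the registry code: "The enrollment site will give the identification number after a patient consents to participate in the registry". Neither distinguishes retrospective from prospective patients, and neither mentions patients who have died or cannot be traced.

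Section 2.5.3 puts a fatal event first among the outcomes: "The mains endpoints collected in this clinical database will be:Sudden cardiac death". The Discussion hopes that the registry will identify patients at risk of fatal ventricular arrhythmia. The Abstract promises "adverse cardiac events at 6 years of follow-up", but no section says whether the 6 years run from CMR, enrolment or consent.

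**The concern.** Taken together, these rules make retrospective entry conditional on survival. A patient scanned in 2006 and approached years later can be registered only if alive and reachable at that time. Between scan and consent, no registered patient can have died; in survival-analysis terms that interval is immortal time.

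The loss is selective. Arrhythmia, ICD implantation or ventricular deterioration in the same interval can still be abstracted, because the survivor consents later and the records exist. Only the fatal endpoint disappears, so its frequency relative to the non-fatal endpoints is distorted as well.

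If a later study counts follow-up from CMR, the denominator includes years in which the event could not be observed, and the sudden-death rate comes out too low. CMR predictors of sudden death would be estimated among those who survived to be asked. Section 2.5.3 provides for de-identified extracts to go to outside proponents, who could not correct this without knowing when each patient consented.

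**Working it through.** The article states no sample size, power or expected event count, so there is no design figure to reproduce. The check sizes the loss from the article's own rate.

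**Inputs from the article**
- Sudden-death rate r = 0.002 per year: "the risk of sudden death has been estimated at around 0.2%/year" (section 1).
- Patients collected so far: 880 (section 3).
- Follow-up horizon: 6 years (Abstract).
- CMR window: 2004 to 2024 (section 2.2).

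**Formula** (constant hazard): P(sudden death within t years) = 1 − exp(−r·t).

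**Step 1. Benchmark.** Six years of complete follow-up: 1 − exp(−0.012) = 1.19%; 880 × 0.01193 = 10.5 sudden deaths.

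**Step 2. Loss by length of the CMR-to-consent gap**

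| Gap (years) | Probability | Per 880 scanned |
|---|---|---|
| 5 | 1.0% | 8.8 |
| 10 | 2.0% | 17.4 |
| 15 | 3.0% | 26.0 |
| 20 | 3.9% | 34.5 |

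This step needs no assumption about calendar dates. It gives the loss if all 880 had that gap, so it must be scaled by the share of patients who are retrospective.

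**Step 3. Illustration for a 6-year window counted from CMR.** Three assumptions are not in the article: CMR dates spread evenly over 2004–2024, every patient followed for the full 6 years, and first approach at the start of the year shown (or at CMR, if later). The years lost per patient are the gap, capped at 6. For 2018, 8/21 = 38% of the window has all 6 years before approach. A further 6/21 = 29% loses half on average. Together that is 38% + 14% = 52%.

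| Approach | Lost of 10.5 | Share lost | Observed | Apparent rate (observed ÷ 5,280 person-years) |
|---|---|---|---|---|
| 2018 | 5.5 | 52% | 5.0 | 0.095%/year |
| 2020 | 6.5 | 62% | 4.0 | 0.076%/year |
| 2022 | 7.5 | 71% | 3.0 | 0.057%/year |
| 2024 | 8.5 | 81% | 2.0 | 0.038%/year |

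Here 5,280 = 880 × 6, ignoring the small loss of person-time to death.

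**Step 4. Sensitivity to the rate.** Section 1 also says "the mortality risk triples after the third postoperative decade". That concerns mortality generally. Applied to sudden death as an upper case (0.6% per year), the 6-year total is about 31, with 16 to 25 lost. The shares are practically unchanged, because they depend on the gap and hardly on the rate.

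**The case against.** The best defence is that this is a condensed article. A waiver or next-of-kin route for deceased patients would normally sit in the full protocol and the local ethics submissions, which are not shown. The consent sentence comes in a paragraph about pseudonymised codes, and the exclusion can be read as covering refusals only. This stands as a reason for caution: a waiver may exist. It does not remove the point, because the article states an unqualified entry rule beside a window opening in 2004. If a waiver exists, that wording misdescribes who enters.

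Second, section 2.5.3 describes a data resource and fixes no survival analysis or time origin. That is true, and the rate bias is therefore conditional on counting from CMR. The missing deaths are not conditional: they follow from the entry rule, and a later analysis plan cannot recover them.

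Third, the variable lists are in figures that are not shown, so an enrolment or consent date may already be collected. Its absence cannot be asserted. What can be asked is that it be released with every dataset.

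Fourth, the size of the gap is unknown. Section 3 gives age at enrolment as 23.5 ± 12 years, and Table 1 gives the same figure as age at the last CMR. This may mean that enrolment is defined as the last CMR, or that the two are close in time. It does not settle the matter.

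A reader might infer more than the text supports:
- *Sudden death is lost as an endpoint.* It is not: deaths after consent are captured, in prospective patients and in retrospective survivors.
- *Only personal consent counts.* The text does not say so, and minors over 10 are eligible.
- *Associations are reversed.* Nothing in the article shows this.
- *A fixed majority of all sudden deaths is missing.* Placing all 880 scans before one consent date in 2018–2023 gives 12.2 to 16.5 lost against 880 × 6 × 0.002 = 10.56 afterwards, or 54–61%. That set-up contains no prospective patients, contrary to section 2.2.

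**Conclusion.** The point holds in limited form. As written, sudden deaths between CMR and consent are not captured in retrospective patients, while non-fatal events in that interval can be. If follow-up is counted from CMR, the sudden-death rate is biased downward and its predictors are estimated in survivors.

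The firmest statement of size is the one by gap: about 9 sudden deaths per 880 for 5 years and 17 for 10 years, against 10.5 expected in 6 years of complete follow-up. It rests on a constant 0.2% per year. The 52–81% range also rests on assumed approach years, evenly spread scans and full 6-year follow-up, and is illustrative only. With so few expected events, even a modest gap matters for this endpoint.

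The conclusion also assumes that no route for deceased patients exists outside the article. If one does, the fault is in the wording of sections 2.4 and 2.5.1.

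**What to change.** 1. In sections 2.5.1 and 2.5.3, require that every released dataset carry the consent date and a retrospective/prospective flag. For fatal endpoints, count risk time from the later of CMR and consent (delayed entry, i.e. left truncation). Non-fatal events before consent remain usable as history, but describe survivors and should be labelled so.
2. Where a site's ethics approval already allows deceased or untraceable patients to be included, correct sections 2.4 and 2.5.1 to say so and count those patients from CMR. Survivors at the same site should then also be counted from CMR: starting only the dead at CMR would bias the rate upward.

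**Cost.** One date and one flag, which may already be held, and a small change to the analysis. The 880 existing records would need the consent date filled in where it is missing. The statistical price is fewer person-years for fatal endpoints and few patients at risk soon after CMR. Delayed entry removes the immortal time but does not restore the missing deaths, and it assumes that the timing of consent is unrelated to prognosis, given the covariates.

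Seeking new waivers at all 18 sites, 8 of them already approved and collecting, or listing every CMR back to 2004, would recover more. Neither is clearly cheap or obtainable, and the correction above does not depend on them.

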#### 2.5.2. Data Collection

The list of variables that will be collected is itemized in Figure 1.

In summary, for each patient, the following will be collected:*Demographic information form;**Baseline information about the patient’s health at the time of enrollment;**Anthropometric data;**Pre-operative anatomy* data: native anatomy impacts the surgical and interventional history of repaired TOF, therefore, when available, the data about the annulus and pulmonary branches anatomy, as well as associated extracardiac defects, will be collected (Figure 2) [17].

*Surgical history*: type and age at intracardiac repair, and previous palliation will also be reported as they influenced the clinical follow-up of this population [2,18].*Electrocardiogram* (ECG) data: QRS length and QRS fragmentation were both identified as risk factors for adverse events in repaired TOF. Moreover, data from Holter monitoring, when available as significant atrial or ventricular arrhythmias, will also be reported (Figure 3) [2,19,20,21].*Transthoracic echocardiography* (TTE) data: TTE is the first diagnostic tool in this population, allowing the evaluation of many of the anatomic and hemodynamic abnormalities in this population [22]. In particular, the current clinical routine is in tricuspid regurgitation and estimated Doppler systolic right ventricular pressure. The main parameters evaluated by TTE, tricuspid annular peak systolic velocity (TAPSE), and myocardial acceleration during isovolumic contraction have also been investigated in evaluating RV function in this population [2,18]. Therefore, data on bi-ventricular and atrial dimensions and function according are included in the dataset of the study.*Cardiac Magnetic Resonance* (CMR) data: CMR is the gold standard. CMR is considered the reference standard for quantifying RV size, function, and PR in patients with repaired TOF [14,15]. Biventricular volumes and function are predictors of adverse outcomes in repaired TOF and atrial volumes, and function also emerged as prognostic predictors. The LGE score also has been demonstrated to be associated with ventricular arrhythmias, and there is an increasing interest in the prognostic role of T1 mapping in this population. Moreover, CMR allows for the evaluation of the anatomy and flow of the main and pulmonary branches, and it is the unique modality that is able to quantify the pulmonary regurgitation and the pulmonary flow distribution. Therefore, all the anatomic and functional parameters evaluated by CMR comprehensively, as well as the evaluation of the aortic valve for regurgitation and measurement of aortic size, are included in the study dataset (Figure 4).*Cardiopulmonary test* (CPET) data: CPET is routinely used in the function evaluation in repaired TOF and provides prognostic predictors in this population. Therefore, any available date, Vo2 mL/kg/min, predicted, Vo2/HR, as well as the type of the protocol used, are included [21,22] (Figure 5).*Cardiac catheterization* (CC) data: CC is mainly restricted in repaired TOF for interventional procedures and when non-invasive evaluation is inconclusive. In case of any cardiac catheterization, the date about atrial and ventricular pressure can be recorded [20,22].*Cardiac tomography* (CT) data: even if a CT scan is rarely indicated in the routine follow-up, in selected cases with contraindication to CMR or for the evaluation of ferromagnetic device, a CT scan could be useful for the evaluation of coronary arteries, conduit calcification. A CT scan may also be considered as an alternative for ventricular quantification in patients unable to undergo CMR [19]. CT data of bi-ventricular and bi-atrial volumes and bi-ventricular function, as well as diameters of great vessels, could be reported.*Brain natriuretic peptides* (Nt-ProBNP and BNP) are prognostic biomarkers in this population and will be also recorded [22,23].
